### Justification of the sample size

On the basis of a previous Famiréa study [18], our hypothesis is that receiving a condolence letter could reduce the risk of presenting symptoms of anxiety/depression (HADS score) by 30 %, diminishing the prevalence at 1 month from 60 % in the group without a condolence letter to 42 % in the group with a condolence letter. In order to detect such a difference between the two groups, with a type I error of 0.05 and a power of 0.80, it is necessary to include 240 family members (120 in each group), that is, 12 inclusions per center in the 22 participating centers (see Additional file 3).

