#### Primary endpoint

The HADS scale (Hospital Anxiety and Depression Scale) — 1 month after the death of the patient.

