### Data analysis

The analysis will be done according to the intention-to-treat principle (that is, each subject will be analyzed in the intervention group to which he (she) was assigned by the randomization, regardless of whether or not it was effectively done). We will report, in each randomization group, summary statistics according to the data (median and interquartile range, percentage with a 95 % confidence interval).

The proportion of family members with symptoms of anxiety/depression at days 30 and 180 will be compared between randomization arms by an exact Fisher test. A comparison of the HADS score distribution will be done using a non-parametric Wilcoxon rank sum test.

A regression model will be used later to search for associated factors should anxiety or depressive syndromes occur, or interactions between intervention effect and family member characteristics, notably the relationship (spouse, child) age, way of life.

Text data will also be analyzed with descriptive methods (factorial analysis of correspondences, word cloud), then predictive methods (text mining).

Statistical analysis will be done on software from SAS (SAS Inc., Cary, NC) and R (http://www.R-project.org/). All the tests will be two-sided with *p*-values of 0.05 or less indicating statistical significance.

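### The stated power of 0.80 at 120 per group does not hold for the planned Fisher's exact test, which gives 0.75, and the same sentence equates 240 with a recruitment plan of 264

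*Protocol article*

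**What the plan says.** In the protocol article, Justification of the sample size assumes that the letter lowers the 1-month prevalence of anxiety/depression symptoms on the HADS "from 60 % in the group without a condolence letter to 42 % in the group with a condolence letter". It then fixes the error rates and the size: "with a type I error of 0.05 and a power of 0.80, it is necessary to include 240 family members (120 in each group"). The sentence goes on to translate this number into recruitment: "that is, 12 inclusions per center in the 22 participating centers". It names no test and points to an additional file, which is not at hand.

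Data analysis names the test. The proportion with symptoms at days 30 and 180 "will be compared between randomization arms by an exact Fisher test". The sidedness is given there too: "All the tests will be two-sided with" a 0.05 threshold. A Wilcoxon rank sum test on the HADS score is planned alongside.

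Primary endpoint gives the HADS scale, "1 month after the death of the patient", without saying whether the score or the proportion is meant.

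**The concern.** The two sections concern the same proportion, time point and significance level, so the stated power should be that of the named test. Fisher's exact test is conservative at these group sizes: its true two-sided error rate lies well under the nominal 0.05, and that costs power. A sample size from an uncorrected large-sample formula makes no allowance for this.

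What is at stake is the chance of detecting the 18-point difference on which the trial is justified. There is also a question of which number of relatives the power statement refers to, because the sentence gives two that differ.

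**Working it through.** **Inputs.** Control 60%, intervention 42%, type I error 0.05, power 0.80, 120 per group, 22 centers with 12 inclusions each (all from Justification of the sample size). Two-sided testing and Fisher's exact test (Data analysis).

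**Step 1: reproduce the plan's figure.** The pooled-variance formula without continuity correction is

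n = [z(0.975)·√(2·p̄·(1−p̄)) + z(0.80)·√(p1(1−p1) + p2(1−p2))]² / (p1−p2)², with p̄ = (0.60 + 0.42)/2 = 0.51.

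- First term: 1.96·√(2·0.51·0.49) = 1.386
- Second term: 0.8416·√(0.24 + 0.2436) = 0.585
- n = (1.386 + 0.585)² / 0.18² = 119.9, so 120 per group

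The same approximation returns a power of 0.8004 at 120 per group. The arcsine formula gives 119.8, so the stated size fits either uncorrected approximation. With a continuity correction, which approximates Fisher's test, the formula gives 131.

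**Step 2: exact power of the planned test.** Take all 121 × 121 possible pairs of counts under Binomial(120, 0.60) and Binomial(120, 0.42). Compute the two-sided Fisher p-value for each pair and add up the probabilities of the pairs with p ≤ 0.05. Do the same for the uncorrected Pearson chi-square test.

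| Evaluable per group | Fisher, exact power | Pearson chi-square, exact power |
|---|---|---|
| 120 | 0.750 | 0.790 |
| 128 | 0.797 | 0.831 |
| 129 | 0.803 | 0.836 |
| 132 | 0.818 | 0.849 |

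Fisher's power first reaches 0.80 at 129 per group (258 in total) and stays at or above it at each size from 129 to 135.

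**Step 3: where the loss comes from.** With 120 per group the true two-sided size of Fisher's test is 0.033 when both arms have 51% and 0.039 when both have 60%. Pearson's test has a true size of about 0.053 when both arms have 60%.

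**Step 4: the recruitment plan.** 22 × 12 = 264, or 132 per group, which is 24 more than 240. At 132 evaluable per group Fisher's power is 0.818. The margin is 132 − 129 = 3 relatives per group, or 3/132 = 2.3%. A fourth loss in each group leaves 128 and a power of 0.797.

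**The case against.** The strongest counter-argument is the recruitment plan itself. The Abstract repeats 12 relatives in each of 22 centers, so the operational target is 264, and Fisher's power there is 0.82, above the stated 0.80. This stands as far as it goes. A reader might infer from the 0.75 that the trial as recruited must fall short of its stated power, and the documents do not support that: the shortfall applies if recruitment stops at 240, or if fewer than 129 per group are evaluable. Equally, the plan does not rescue the statement. The article calls 240 necessary, treats it as equivalent to 22 × 12, and gives the extra 24 no purpose. If they are meant to cover losses to the day-30 telephone call, they cannot also pay for the choice of test.

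A second argument is that the mismatch is mild. Fisher's test protects the type I error, and the planning rates are no more certain than the power: with 41% instead of 42% in the intervention group, Fisher's power at 120 per group would be 0.798. This also stands and bears on the weight of the point. A reader might take the conservatism as a flaw in the analysis, but it introduces no bias and no excess of false positives.

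Third, no test is named in the sample size section, so the use of an uncorrected chi-square formula is inferred from the matching number. That is so, but the 0.75 does not depend on the inference. It follows from the stated rates, size and test alone.

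Finally, a Wilcoxon test on the score is also planned, and Primary endpoint does not settle which comparison leads. The sample size rests on the proportion, however, and Fisher's test is assigned to that proportion, so the power of another test on another summary cannot support the figure.

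**Conclusion.** The power statement is wrong as written, with moderate severity. For 60% against 42% with 120 evaluable relatives per group, the planned test has power 0.75, not 0.80, which is a type II error of 25% against 20%. The arithmetic behind 120 is not faulty in itself: it reproduces under an uncorrected approximation, but it does not describe the test that Data analysis names. Reaching 0.80 with Fisher's test takes 129 evaluable per group. The 131 from the continuity-corrected formula is an approximation and slightly overstates the need.

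The conclusion assumes independent binomial outcomes, equal groups, the article's own rates, no adjustment for center, and complete day-30 data at the sizes shown. The conflict between 240 and 264 belongs to the same point, because it decides whether the power of the planned analysis is 0.75 or, with all relatives evaluable, 0.82.

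**What to change.** One of two changes, each a sentence or so and neither requiring more relatives than the 12 per center already planned.

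- **Keep Fisher's test.** Restate the power in Justification of the sample size as 0.75 with 120 evaluable per group and 0.82 with 132. The cost is a less favourable figure at 240.
- **Change the test.** Name the uncorrected chi-square test for the day-30 proportion in Data analysis and state its exact power, 0.79 at 120 per group. The cost is a true size that can slightly exceed 0.05 (about 0.053). Because Trial status reports that recruitment is under way, this must be fixed before any unblinded look at outcomes.

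In either case, reconcile 240 with 22 × 12 = 264 in the same sentence: say which is the recruitment target, and whether the additional 24 are meant for losses, for the test, or for neither.

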**Methods/design:**

This is a randomized, controlled, multicenter study. Research will compare two groups of bereaved family members: one group that does not receive a condolence letter (control) and one group that receives a condolence letter 15 days after the death (intervention). Each of the 22 participating centers will include 12 relatives. Participating relatives will be followed up by phone with a call at 1 month and one at 6 months to complete questionnaires, permitting evaluation of post-ICU burden. The main outcome is anxiety and depression measured at 1 month. Other outcomes include evaluation of quality of dying and death, post-traumatic stress, and complicated grief.

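### The sample size section equates 240 relatives with 12 inclusions in each of 22 centers, which is 264, and does not explain the extra 24

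*Protocol article*

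**What the plan says.** The protocol article gives the planning assumptions under Justification of the sample size: "diminishing the prevalence at 1 month from 60 % in the group without a condolence letter" "to 42 % in the group with a condolence letter", "with a type I error of 0.05 and a power of 0.80". Data analysis adds "All the tests will be two-sided" and names Fisher's exact test for comparing the proportions.

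The resulting target is "it is necessary to include 240 family members (120 in each group), that is, 12 inclusions per center in the 22 participating centers". The sentence then points to Additional file 3, which is not among the documents at hand. The Methods/design part of the abstract gives only the quota: "Each of the 22 participating centers will include 12 relatives".

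The primary endpoint, the HADS at 1 month, is collected by telephone at day 30 (Design). Trial status says that recruitment is under way.

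**The concern.** The sentence offers the total and the center quota as the same number, and they are not. Since the abstract repeats the quota, the 264 is unlikely to be a stray misprint in one place. A reader of the article cannot tell whether recruitment is meant to end at 240 or at 264, or whether 240 counts relatives randomized or relatives with a usable day-30 HADS.

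What is at stake is the match between the stated power and the number enrolled. If 240 is a cap on inclusions, every relative not reached at day 30 takes the analysis below the size on which the 0.80 rests. If all centers fill their quota, there is room for some losses, but the article does not say that this is the purpose.

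**Working it through.** **Inputs.** Control proportion p1 = 0.60, intervention proportion p2 = 0.42, type I error 0.05, power 0.80, two groups of 120, 22 centers and 12 per center (Justification of the sample size); two-sided testing and Fisher's exact test (Data analysis).

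**1. Reproduce the stated 240.** Pooled-variance normal approximation, no continuity correction, with p̄ = (0.60 + 0.42)/2 = 0.51:

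n per group = [1.960 × √(2 × 0.51 × 0.49) + 0.842 × √(0.60 × 0.40 + 0.42 × 0.58)]² / (0.60 − 0.42)²

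= [1.960 × 0.7070 + 0.842 × 0.6954]² / 0.0324 = (1.971)² / 0.0324 ≈ 119.9, so 120 per group and 240 in total. This matches exactly.

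**2. Work out the quota.**

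- 12 × 22 = 264, or 132 per group.
- 264 − 240 = 24, and 24/240 = 10%.
- 240/22 = 10.9 per center, and 11 × 22 = 242.
- 240/12 = 20 centers, not 22.

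Rounding up to whole relatives per center would give 11, so rounding does not explain 12.

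**3. Power at each target with complete data, 60% against 42%.**

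| Total | Per group | Normal approximation | Fisher exact (full enumeration) |
|---|---|---|---|
| 240 | 120 | 0.800 | 0.750 |
| 264 | 132 | 0.837 | 0.818 |

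**4. What the 24 could be.** If 264 are randomized, 240 remain after a loss of 24/264 = 9.1%. Equally, 240 × 1.10 = 264. The continuity-corrected sample size is 131 per group, 262 in total, which 12 per center would also cover. Each reading fits, and the text shown supports none of them over the others.

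**5. Sensitivity to losses.** The article gives no loss rate, so the rates below are assumptions. Power is by the normal approximation.

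| Assumed share without day-30 HADS | 240 randomized | 264 randomized |
|---|---|---|
| 5% | 0.780 | 0.818 |
| 10% | 0.757 | 0.796 |
| 20% | 0.707 | 0.748 |

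At a given loss rate, the choice between the two targets is worth about 0.04 in power.

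**The case against.** The strongest reply is that 240 is the required number, correctly derived, and that 12 per center in 22 centers is the only operational quota, stated the same way in both places. No passage says that recruitment stops at 240. Filling the quota gives more than the requirement, so the slip errs on the safe side. An article also condenses a fuller protocol, and Additional file 3, cited in the same sentence, may explain the surplus.

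Much of this stands. A missing allowance for losses is not a finding here, because an article may leave it to the full protocol or the additional file. The reply does not rescue the sentence itself, which declares two unequal figures equal, whatever another file may say.

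A reader might go further and infer that the power is undefined, that 240 is wrong, or that a loss allowance has been concealed. The documents support none of these. Power is stated and reproduces at 0.80 for 240, 240 is the right output of the stated inputs, and nothing shows that an allowance exists. A reader might also quote a power near 0.71 for 240 inclusions (Fisher, assumed 10% loss, 108 per group) as the cost of the discrepancy. Most of that fall has other sources: 0.80 to 0.75 comes from using Fisher's test instead of the normal approximation, and 0.75 to 0.71 from the assumed loss.

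**Conclusion.** The point holds as a contradiction in a stated figure. The sample size section equates 240 (120 per group) with a quota that yields 264 (132 per group), the abstract repeats that quota, and the 24 extra relatives are unexplained in the text shown. The required size of 240 is correct for its inputs.

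With complete data, the choice of target moves power from 0.80 to 0.84 by the normal approximation and from 0.75 to 0.82 under the planned Fisher test. Under the named test, then, the stated 0.80 is reached at 264 but not at 240. These values rest on the article's own 60% and 42%; only the loss table uses outside assumptions. The matter is of moderate weight: it affects the recruitment target and how the stated power is read, but not the endpoint, the allocation or the planned test.

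**What to change.** Rewrite the sentence with one recruitment target and a meaning for each figure, and bring the abstract into line. There are two consistent versions:

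- **264 randomized.** State that 12 relatives in each of 22 centers will be randomized and that 240 (120 per group) is the number required for analysis. The sponsor must confirm whether the other 24 (9% of 264) are an allowance for relatives without a day-30 HADS. That reason should not be written in unless it was the intention.
- **240 randomized.** Correct the quota to about 11 per center in both places, and restate the power for the number expected to have a day-30 HADS, giving the assumed loss rate.

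In either version, say which method produced the 0.80, since the planned Fisher test gives a different value at the same size.

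The first version costs wording only, because the quota is already the stated plan. The second also needs a revised power statement and notice to the centers. Neither changes the design. The correction should be made before recruitment ends.

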### Ethics

The study was approved by our local IRB (Comité de protection des personnes CPP Ile de France IV, Saint Louis, number 2014/14SC), the CNIL (Commission Nationale de l’Informatique et des Libertés), responsible for ensuring that information technology remains at the service of citizens, number MMS/VCS/AR 149697, and the CCTIRS (Comité Consultatif sur les Traitements de l’Information en matière de Recherche dans le domaine de la Santé), number 14.284.

## Discussion

This study will allow us to examine if sending a condolence letter can reduce the risks of presenting symptoms of anxiety and depression, complicated grief and symptoms of PTSD after a death in the ICU. If the result is positive, it would be possible to open this practice to all ICUs so as to help families in this sometimes complex and painful process. This practice has no financial costs. Reducing rates of anxiety, depression, post-traumatic stress, and complicated grief after a death in the ICU is important as a public health issue: people suffering from these symptoms require medical care, follow-up, and treatment. Reducing the rate of post-ICU burden would allow a reduction of medical consultations and treatments. The results of the study would allow other hospital units to reflect on putting a similar strategy in place.

### Trial status

The trial is currently recruiting patients. Inclusion started on 1 December 2014.

## Abbreviations

HADS: Hospital Anxiety and Depression Scale
ICG: Inventory of Complicated Grief
ICU: intensive care unit
IES-R: Impact of Event Scale-Revised
